### Interventions

Two types of CKD care programs will be provided separately according to their respective district of residence. CKD patients residing in district No.8 will be assigned to the control group and those in district No.5 will be assigned to the intervention group (Figure 3). It should be noted that medical facilities in these 2 district hospitals are quite comparable (Table 1). Three investigators who are nephrologists [[name], [name], [name]], will provide essential knowledge about CKD care and treatments according to NKF-K/DOQI guidelines to all staffs of both groups [9].

**Figure 3 F3:**
[figure not shown]
Design of the study.

In the control group, two general practitioners and two chronic care nurses will provide CKD care to the subjects according to treatment guidelines (Table 2). All medical cares and educational programs will be provided during their visit to the district hospital. Educational activities will be provided as group counseling. The educational topics will be arranged sequentially i.e. basic knowledge about CKD, optimal diet for pre-dialysis CKD patients, effect of hypertension on CKD, relationship between diabetes mellitus and CKD, drug use in CKD, and renal replacement therapy.

**Table 2 T2:** **Treatment guidelines for both treatment groups **[8]

**Clinical and laboratory parameters**	**Treatment targets**
Blood pressure	Less than 130/80 mmHg
Body mass index	18.5-24.9 kg/m^2^
Hemoglobin	More than 10 g/dl
HbA1C	Less than 7%
LDL-cholesterol	Less than 100 mg/dl
Serum bicarbonate	More than 22 mEq/L
Urine protein-creatinine ratio	Less than 500 mg/g
Sodium intake	Less than 2,400 mg/day
Protein intake	Less than 0.8 g/kg ideal body weight /day
Smoking	Smoking cessation
Physical exercise	30 minutes or more per day 3 times a week

#### **
*Integrated CKD care program*
**

In the intervention group, an integrated CKD care program (ICP) will be implemented. The ICP is a collaborative CKD care program. The key process is the cooperation between multidisciplinary team (MDT) and community CKD care network (CCN). The MDT consists of two general practitioners, two chronic care nurses, one pharmacist, one nutritionist, and one physical therapist. Each CCN subgroup consists of 1 subdistrict health care officer, 3–5 VHVs, and family members of the CKD patients residing in the respective patient subdistrict.

In the pre-study period, a 4-day CKD care training-course will be organized for members of CCN before commencement of the intervention program. The training-course contents include basic knowledge of CKD, NKF-K/DOQI guidelines, and optimal diet for CKD patients. The contents has been simplified to match with their basic medical knowledges. Two dietitians [[name], [name]] will provide essential knowledge about collection and interpretation methods of modified 24-h dietary recalls or Easy Dietary Assessment tool (EDA) [13]. CCN members must pass Pre/Post test evaluation with a minimum score of 75 percent preceeding commencement of the program.

### Clinical and laboratory assessments

Patients in both groups will be scheduled to follow-up at their respective district hospitals at every 3 months. During each hospital visit, blood pressure, body weight, and waist circumference will be assessed. Laboratory measurement will be done at enrollment, the first month and every 3 months thereafter or when patients are withdrawn from the study (Table 4). Blood pressure will be recorded twice with a sphygmomanometer with a 15-minute rest interval. The ACEi/ARBs dosages will be adjusted by the caring physicians. In case of any patient develops intolerable side-effects of ACEi/ARBs, other antihypertensive agents will be substituted.

**Table 4 T4:** Schedule of clinical and laboratory assessments during the study period

**Visit**	**Screening period**	**Visit 1**	**Visit 2**	**Visit 3**	**Visit 4**	**Visit 5**	**Visit 6**	**Visit 7**	**Visit 8**	**Visit 9**	**Visit 10**
**Month**		**0**	**1**	**3**	**6**	**9**	**12**	**15**	**18**	**21**	**24**
Blood pressure, body weight, waist circumference	√	√	√	√	√	√	√	√	√	√	√
Serum creatinine	√	√	√	√	√	√	√	√	√	√	√
eGFR	√	√	√	√	√	√	√	√	√	√	√
Serum potassium	-	-	√	-	√	-	√	-	√	-	√
Phosphate, Calcium, Albumin	-	√	-	-	√	-	√	-	√	-	√
Hemoglobin	-	√	-	-	√	-	√	-	√	-	√
HbA1C	-	√	-	-	√	-	√	-	√	-	√
LDL-cholesterol	-	√	-	-	√	-	√	-	√	-	√
Urine dipstick protein	-	√	-	-	√	-	√	-	√	-	√
Urine protein -creatinine ratio	-	√	-	√	√	√	√	√	√	√	√
24-hour Urine for Na, Urea-N, Creatinine, Protein	-	√	-	-	√	-	√	-	√	-	√

### Laboratory analysis

A protocol of laboratory investigation is summarized in Table 4. Prior to each hospital visit, all subjects will be instructed to have an 8-hour overnight fast. Plasma glucose, lipid profile, HbA1C, albumin, electrolytes, and urine analysis will be measured in the next morning. After centrifugation, plasma and urine samples will be centrifuged and transported at 4°C and analyzed within 24 hours at the laboratory Department of the District 2 Hospital. All blood chemistries will be measured with ABX Pentra 400 analyzer (HORIBA ABX S.A.S., France). Urine protein and creatinine will be measured with the pyrogallol red colorimetric method with the same analyzer. All biochemistry analyses will be validated according to the standard protocol of Department of Medical Sciences, Ministry of Public Health, Thailand. Serum creatinine will be measured by the enzymatic method. Serum creatinine measurement will be standardized with standard reference material (SRM 967) by commutability study at every 6 months [14].

Two out of twelve subgroups of both groups will be randomly selected and assigned to collect 24-hour urine. An aliquot of 24-hour urine of each sample will be sent for urine chemistry analysis protein, creatinine, urea, and sodium at Laboratory Department of Division of Nephrology, Chulalongkorn University, Bangkok, Thailand.

### Outcomes

The primary outcome of this study is the difference of rate of eGFR decline. The secondary outcomes are laboratory parameters (Table 4) and incidence of clinical endpoints including all-cause mortality, cardiovascular events (acute myocardial infarction and stroke), ESRD (eGFR is less than 15 ml/min/1.73 m^2^), and 50% increase in serum creatinine from baseline. In this study, acute myocardial infarction is defined as a new ischemic pattern change of ECG and significant rising of cardiac enzymes. Acute stroke is defined as there is a clinical significant neurological deficit with an objective evidence by appropriate imaging study (e.g. computerized tomography scan). Patients will be followed at the first month and every three months after enrollment. Subgroup analysis will be done for selected parameters including age, sex, and diabetes mellitus. Quality of life will be assessed using a validated questionnaire, Thai SF-36 health survey [15].

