## Methods

### Study design

The ESCORT study is a community-based, cluster randomized controlled trial. Duration of the study is 2 years. This study has been conducted at Kamphaeng Phet Province, located about 400 kilometers north of Bangkok (Figure 1 and Figure 2). Due to strong relationship among neighboring households in rural communities, it is unable to assign subjects living in the same district to be randomly received either of the 2 CKD care programs without crossover interference from one subject in one household to another. As a result, we have conducted a cluster randomized controlled trial. Two out of eleven districts of the Province, namely Sai Thong Wattana District (control group) and Khlong Khlung District (intervention group), were randomly selected. Details of Public health characteristics of these 2 districts were described in Table 1.

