### Enrollment

The study was approved by the Ethics Committee of Institutional Review Board of Ministry of Public Health, Thailand and was registered with http://www.clinicaltrials.gov (NCT01978951). Written inform consents were obtained prior to recruitment. The study was conducted in accordance with good clinical practice and the Declaration of Helsinki [7]. Eligible cases are those who live in these 2 districts, age of 18–70 years old and had diabetes and/or hypertension. Patients whose eGFR was in a range of 15–59 ml/min/1.73 m^2^ body surface area estimated twice at 3 months apart were asked to participate in this study. Creatinine-based estimated glomerular filtration rate (eGFR) was calculated with the CKD-EPI equation [8]. Patients were excluded if they have any of the following: unstable/advanced cardiovascular disease, obstructive uropathy, ESRD, HIV infection, pregnancy, body mass index (BMI) less than 18 or more than 40 kg/m^2^, being under treatment for malignancy, urine protein-creatinine ratio more than 3.5 g/g creatinine and active urinary sediment (urine red blood cells more than 3 cells/high power field or urine white blood cells more than 10 cells/high power field). Hypertension was defined as a systolic blood pressure higher than 140 mmHg or a diastolic blood pressure higher than 90 mmHg or concomitant use of antihypertensive medications [9]. Blood pressure was recorded twice with a sphygmomanometer with 15-minute rest between the measurements. Diabetes was diagnosed when a fasting plasma glucose is at or above 126 mg/dl or HbA1C at or above 6.5 percent twice after repeated measurements [10].

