### Sample size

In a previous observational study, the rate of eGFR decline among diabetic patients with overt nephropathy was 4.2 ± 3.8 ml/min/1.73 m^2^ BSA per year [11]. We hypothesized that if the rate of eGFR decline of intervention group is less than control group at least 1 ml/min/1.73 m^2^ per year, the primary outcome of the study will be interpreted as significant. To acheive 80 percent or higher power to detect the difference between the two treatments, it was estimated that 228 stage 3–4 CKD patients were needed to be enrolled to each group [12]. Taking into account that 15% of patients might be loss to follow-up because of non–end point death or other reasons, approximately 250 patients for each group were required.

According to the inclusion and exclusion criteria, recruitment had done in January to June 2011. About 25% of candidates were eligible and asked to participate in the study. The main reason for non-participation was inability of the patient and caregiver to attend the anticipated visits. In July 2011, 433 patients had been enrolled . Enrolled subjects of each group will be further subdivided into 12 patient subgroups with respect to the vicinity of their subdistrict. Each subgroup will consist of 25–30 CKD patients.

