### Statistical analysis

Analysis of the primary outcome will be based on an intention-to-treat basis. Descriptive statistics will be expressed as the mean and standard deviation. Discrete variables will be presented as frequency and percentage. An independent t-test will be applied to compare mean values and mean differences between intervention and control groups. Differences between categorical variables will be analysed with Chi-square or Fisher’s exact tests. The comparison of the rate of eGFR decline will be analyzed using linear mixed models (Generalized Estimating Equation) [16]. The difference of incidence of clinical endpoints will be analysis using Cox-regression analysis. All statistical tests will be two-tailed tests. A P-value of less than 0.05 will be considered statistically significant. The data will be analysed using SPSS 16.0 (SPSS Inc., Chicago, IL, USA).

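### ESRD is defined only as eGFR below 15, which is also the entry floor, with no persistence rule and no renal replacement therapy, so one passing low value can count as an event

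*Protocol article*

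**What the plan says.** Four parts of the protocol article bear on this point.

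- **Outcomes** gives the renal endpoints as "ESRD (eGFR is less than 15 ml/min/1.73 m^2^), and 50% increase in serum creatinine from baseline". No second value, minimum duration, dialysis or transplantation is mentioned. Infarction and stroke, in the same section, each need supporting objective evidence.
- **Enrollment** admits "Patients whose eGFR was in a range of 15–59 ml/min/1.73 m^2^ body surface area estimated twice at 3 months apart". The lowest eligible value is therefore the event threshold, and entry requires two values where the endpoint names none.
- **Clinical and laboratory assessments** states: "Laboratory measurement will be done at enrollment, the first month and every 3 months thereafter or when patients are withdrawn from the study (Table 4". Table 4 shows creatinine and eGFR at months 1, 3, 6, 9, 12, 15, 18, 21 and 24, which is nine values after baseline.
- **Statistical analysis** says: "The difference of incidence of clinical endpoints will be analysis using Cox-regression analysis".

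Renal replacement therapy appears only under Interventions, as a teaching topic for the control group.

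**The concern.** ESRD is meant to be an irreversible state. A time-to-event analysis takes the first qualifying value, and nine values give nine chances for measurement error or a short acute episode to cross the line. A patient who enters just above 15 and does not deteriorate can be counted as having reached ESRD.

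False events of this kind carry no information on the treatment, so they pull the hazard ratio toward 1. In the other direction, a patient who starts dialysis without a recorded value below 15 is not an event at all, and eGFR measured after dialysis starts no longer describes kidney function.

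**Working it through.** **The document's own figure.** Only the sample size can be reproduced, and it confirms how to read the decline. Sample size gives "the rate of eGFR decline among diabetic patients with overt nephropathy was 4.2 ± 3.8 ml/min/1.73 m^2^ BSA per year" and a difference of 1. Then n = 2 × (1.96 + 0.842)² × 3.8² / 1² = 2 × 7.85 × 14.44 ≈ 227 per group. The t-test version gives 227.6, so 228, as stated. The 3.8 is thus used as the between-patient SD. No event rate is given for ESRD.

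**Step 1: a patient with no true decline.** Let g be the true eGFR. The within-person CV is not in the document and is assumed to be 5%, 7.5% or 10%. With independent normal errors, the chance that one reading is below 15 is p = Φ((15 − g)/(CV × g)), and the chance of at least one in nine is 1 − (1 − p)⁹.

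Example: g = 17 and CV 7.5% give (15 − 17)/1.275 = −1.569, p = 0.058, and 1 − 0.942⁹ = 42%.

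The last column is simulated, given that both entry values are at least 15.

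| True eGFR | At least one of nine below 15 (CV 5 / 7.5 / 10%) | Two consecutive below 15 |
|---|---|---|
| 16 | 63 / 87 / 94% | 8 / 25 / 39% |
| 17 | 8 / 42 / 68% | 0.1 / 2.6 / 10% |
| 18 | 0.4 / 11 / 36% | 0.0 / 0.1 / 1.7% |
| 20 | 0.0 / 0.4 / 5.5% | about 0% |
| 25 | about 0% | about 0% |

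For a stable patient the problem is confined to entry at about 15–18, with a small tail to 20.

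**Step 2: the whole cohort.** Each simulated patient has a linear decline drawn from 4.2 ± 3.8 per year, log-normal errors, two entry values in 15–59 and the nine visits of Table 4. The baseline distribution is assumed: uniform over 12–62, or normal with mean 40 and SD 11. A false event is a reading below 15 in a patient whose true value is never below 15 at any visit.

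| CV 5 / 7.5 / 10% | Uniform baseline | Normal baseline |
|---|---|---|
| Counted by one value | 20.4 / 21.0 / 21.8% | 10.4 / 10.7 / 11.2% |
| False, of all patients | 0.8 / 1.5 / 2.2% | 0.5 / 0.9 / 1.4% |
| False, of counted events | 4 / 7 / 10% | 5 / 8 / 12% |
| False events removed by confirmation | 0.8 / 1.3 / 2.0% | 0.5 / 0.8 / 1.3% |
| True crossings no longer counted | 2.3 / 2.4 / 2.6% | 2.0 / 2.0 / 2.1% |

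Normal instead of log-normal errors raise the upper ends to 2.6% of patients and 14% of counted events. For the 433 patients reported as enrolled, 0.5–2.2% is about 2 to 10 people (433 × 0.005 = 2.2; 433 × 0.022 = 9.5). Once decline is included, patients who drift down to 15–18 during follow-up share the risk with those who entered there.

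**Step 3: the 50% creatinine rise.** Assume a creatinine CV of 4–8% at baseline and at follow-up. The log ratio has SD about √2 × 0.08 = 0.113 at the upper end, and ln 1.5 = 0.405, so z = 3.6 and p ≈ 0.00017. Over nine visits this is at most 9 × 0.00017 ≈ 0.15%, and nearly nil at 4%. Noise alone does not produce this endpoint. Transient acute rises could, but the document gives no frequency for them.

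**The case against.** - **The text does not say that a single value suffices.** It gives a threshold and is silent on confirmation, which a full protocol or SAP might add. This stands as a limit on wording. But the article writes the definition out, and as written the first low value qualifies.
- **The large percentages describe a narrow group.** This stands. A reader might infer from Step 1 that most ESRD events would be noise. The cohort figures do not support that: most counted patients truly cross.
- **Confirmation loses more true events than it removes false ones.** This also stands in every setting of Step 2. However, about 1.6–2.0 of the 2.0–2.6 percentage points are patients whose only low reading is at month 24. The effect is close to ending event ascertainment one visit early. That costs power, whereas false events dilute the hazard ratio.
- **The dialysis gap is narrow.** Visits are three-monthly and a sample is taken at withdrawal, so most patients starting dialysis would already have a value below 15. This stands. The gap concerns starts between visits, after missed visits, or at 15 or above.
- **Bias between arms is not shown.** A reader might infer it, because one district forms each arm. It would follow only if the districts enrolled different shares of patients near 15, and the document does not indicate that they did.

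**Conclusion.** The point holds as a weakness in the definition of a secondary endpoint. ESRD is fixed at the entry floor with neither persistence nor renal replacement therapy, so a literal count includes some events that are noise or reversible. The expected size is about 0.5–2% of patients, roughly 4–12% of counted ESRD. This rests on an assumed CV of 5–10%, independent errors, assumed baseline distributions and the document's decline of 4.2 ± 3.8, which came from diabetic patients with overt nephropathy. Transient acute episodes are not in the model and would add to it.

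A reader might go further and doubt the main result. The document does not support that: the primary outcome is the rate of eGFR decline, and neither it nor the sample size uses this definition. Nor does measurement noise undermine the 50% creatinine endpoint.

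**What to change.** For the analysis, define ESRD as either of the following, dated at the first qualifying value or at the start of therapy:

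- eGFR below 15, confirmed at the next scheduled visit or at the withdrawal measurement;
- start of long-term renal replacement therapy.

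Report the single-value definition as a sensitivity analysis. Apply the same confirmation to the 50% creatinine rise, giving the exclusion of transient acute rises as the reason.

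No additional creatinine samples are needed, since every visit already has one; starts of renal replacement therapy must be recorded. The price is that late crossings, above all a first crossing at month 24, stay unconfirmed. Under the assumptions above, about 2–2.6% of patients with a true crossing would not be counted (433 × 0.020 = 8.7 to 433 × 0.026 = 11.3, so about 9 to 11 people), with some loss of power. The sensitivity analysis shows whether that matters.

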### Statistical analysis

Analysis of the primary outcome will be based on an intention-to-treat basis. Descriptive statistics will be expressed as the mean and standard deviation. Discrete variables will be presented as frequency and percentage. An independent t-test will be applied to compare mean values and mean differences between intervention and control groups. Differences between categorical variables will be analysed with Chi-square or Fisher’s exact tests. The comparison of the rate of eGFR decline will be analyzed using linear mixed models (Generalized Estimating Equation) [16]. The difference of incidence of clinical endpoints will be analysis using Cox-regression analysis. All statistical tests will be two-tailed tests. A P-value of less than 0.05 will be considered statistically significant. The data will be analysed using SPSS 16.0 (SPSS Inc., Chicago, IL, USA).

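### The t-test, Chi-square/Fisher and Cox analyses treat patients as independent, and the primary model names no cluster level, in a trial allocated by district and delivered by subgroup teams

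*Protocol article*

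**What the plan says.** **Allocation.** Under Study design the protocol article calls the trial cluster randomized and explains why patients in one district could not be split: "Due to strong relationship among neighboring households in rural communities", crossover between the two programmes could not be prevented. It then states: "Two out of eleven districts of the Province, namely Sai Thong Wattana District (control group) and Khlong Khlung District (intervention group), were randomly selected". Interventions confirms that residence decides treatment: "CKD patients residing in district No.8 will be assigned to the control group and those in district No.5 will be assigned to the intervention group".

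**Subgroups and delivery.** Under Sample size: "Enrolled subjects of each group will be further subdivided into 12 patient subgroups with respect to the vicinity of their subdistrict", and "Each subgroup will consist of 25–30 CKD patients". In the intervention arm, the Integrated CKD care program section describes the local team: "Each CCN subgroup consists of 1 subdistrict health care officer, 3–5 VHVs, and family members of the CKD patients". That team makes the home visits to its own patients, covering diet, blood pressure, medication and exercise. Table 3 gives the control group a yearly home visit and the intervention group quarterly visits.

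**Analysis.** Under Statistical analysis: "An independent t-test will be applied to compare mean values and mean differences between intervention and control groups". Categorical variables get Chi-square or Fisher's exact tests. For events: "The difference of incidence of clinical endpoints will be analysis using Cox-regression analysis". The rate of eGFR decline, the primary outcome, is to be compared with linear mixed models, with generalized estimating equations given in brackets. No unit of correlation is named for any of these analyses. All tests are two-sided at 5%.

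**The concern.** The reason given for allocating by district is that neighbours influence one another. For the same reason, outcomes of neighbouring patients are likely to be correlated. In the intervention arm a shared officer and shared volunteers add a second source of correlation. A t-test, a Chi-square or Fisher test and an ordinary Cox model all take patients as independent. With positive correlation inside subgroups, their standard errors are too small, their intervals too narrow and their P-values too low.

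The outcomes most exposed are those the local team acts on directly: blood pressure, diet-related laboratory values and, through them, clinical events. For the primary outcome, the method named can handle correlated data, but which correlation it will handle is left open.

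**Working it through.** **1. The plan's own sample size.** Inputs from Sample size: difference 1, SD 3.8 (both ml/min/1.73 m² per year), power 80%. From Statistical analysis: two-sided 5%.

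n per arm = 2 × (1.960 + 0.842)² × 3.8² / 1² = 226.7, so 227. The t-based version gives 227.6, so 228, which is the stated figure. It is reproduced by the formula for independent patients, with a design effect of 1, and the section mentions no ICC or inflation. Planning and the named secondary tests therefore rest on the same assumption.

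**2. Cluster size.** There are 12 subgroups per group, 24 in all. With 433 enrolled, m = 433/24 = 18.0. The stated 25–30 per subgroup would need 24 × 25 = 600 to 24 × 30 = 720 patients. That does not fit the 433 enrolled, so m = 18 is used as the main case. The split of the 433 by arm is not given, so equal arms are assumed.

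**3. True error of an unadjusted test.** The ICC is not in the document; 0.01 to 0.05 is an assumption. Design effect DE = 1 + (m − 1) × ICC. The true standard error is √DE times the unadjusted one, and the true error of a nominal 5% test is 2 × [1 − Φ(1.96/√DE)].

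| ICC, both arms, m = 18.04 | DE | √DE | True error |
|---|---|---|---|
| 0.01 | 1.170 | 1.08 | 7.0% |
| 0.02 | 1.341 | 1.16 | 9.1% |
| 0.05 | 1.852 | 1.36 | 15.0% |

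**4. How far this depends on the assumptions.**

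- *Correlation in the intervention arm only.* The average of 1 and DE is (1 + 1.170)/2 = 1.085 at ICC 0.01 and (1 + 1.852)/2 = 1.426 at ICC 0.05. The true error is 6.0% to 10.1%.
- *After the 15% loss the plan allows for.* 433 × 0.85 = 368 patients, m = 368/24 = 15.3, DE 1.143 to 1.717. The true error is 6.7% to 13.5%.
- *Stated subgroup size of 25–30.* DE is 1.24 to 1.29 at ICC 0.01 and 2.20 to 2.45 at ICC 0.05. The true error is 7.8% to 21.1%, but enrolment does not support this size.
- *Subdistrict as the cluster.* Table 1 gives 3 subdistricts in the control district and 10 in the intervention district. With 184 per arm (368/2), m is 61.3 and 18.4. The DEs are 1.603 and 1.174 at ICC 0.01 (average 1.389), and 4.017 and 1.870 at ICC 0.05 (average 2.943). The true error is 9.6% to 25.3%.

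**5. Degrees of freedom.** A comparison on subgroup means has 24 − 2 = 22 degrees of freedom. For 24-hour urine, Laboratory analysis restricts collection to two of the twelve subgroups in each group. That leaves 4 − 2 = 2 degrees of freedom, with a two-sided 5% critical t of 4.30 instead of about 2. A t-test on some 2 × 18 = 36 patients per group would hide this.

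**6. District level.** There is one district per arm, so 2 − 2 = 0 degrees of freedom between districts within arms. The district variance cannot be estimated from the trial, whatever model is used.

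**The case against.** The strongest objection concerns the primary outcome. A mixed model or GEE is a method for correlated data, and an article may leave its random effects or working unit to a fuller plan that is not shown. A reader might infer that every planned test ignores clustering and that the error rate of the primary slope comparison is inflated. The document does not support that. The model could carry a subgroup term. If its unit is only the patient's repeated eGFR values, subgroup correlation is missed. If the unit is the district, there are two clusters, too few for a robust variance. The text does not say which applies, so for the primary outcome the level is unspecified and has not been shown to be ignored.

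This defence does not extend to the other analyses. There the article names specific tests, the first of them an independent-samples test, and independence is what the Study design section gives reason to doubt.

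The second objection is about size. The ICC is assumed, a single range is applied to slopes, laboratory values and events, and the shared-team mechanism is strongest in the intervention arm. This stands, and it is why the intervention-only figures are shown. They are a lower case, because ties between neighbours may also act in the control district. The direction of the error does not depend on the ICC chosen, as long as it is above zero.

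The third objection is that subgroups were not randomized, so a subgroup-adjusted test could look sound while the comparison still rests on two districts. This also stands. The adjustment is needed but is not sufficient.

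**Conclusion.** The point holds in this form. As written, the t-test, Chi-square/Fisher and Cox analyses treat patients as independent, against the trial's own rationale for its design and its mode of delivery. The primary model needs its cluster level stated.

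For an assumed subgroup ICC of 0.01 to 0.05 in both arms, equal arms and 18 patients per subgroup, an unadjusted 5% test has a true error of about 7% to 15%. If only the intervention arm is clustered, it is about 6% to 10%. These figures apply to the unadjusted tests. They would apply to the primary comparison only if its model turned out to ignore subgroups.

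A reader might also infer that a subgroup term makes the between-arm comparison valid. It does not: it deals with correlation inside districts, while the difference between the two districts stays fully confounded with treatment.

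**What to change.** Change the Statistical analysis section as follows.

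1. **Primary outcome.** State one model and its levels: repeated eGFR values within patient, patients within subgroup, with a random subgroup intercept and slope and small-sample degrees of freedom of about 22.
2. **Means and proportions.** Replace the t, Chi-square and Fisher comparisons of outcomes by linear or logistic models with a subgroup effect, or by a test on the 24 subgroup means or proportions.
3. **Clinical endpoints.** Use a subgroup-robust variance or a shared frailty in the Cox model.
4. **24-hour urine outcomes.** Report them descriptively, or with about 2 degrees of freedom and that limit stated.
5. **Sensitivity analysis.** Repeat with subdistrict (3 vs 10) as the cluster; this leaves 13 − 2 = 11 degrees of freedom.
6. **Limitation.** State that none of these steps removes the district effect, which is fully confounded with treatment.

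The cost is analysis wording, wider intervals, and keeping subgroup and subdistrict membership in the analysis data set. The article does not say that membership is recorded for analysis, so this should be confirmed. It should also be checked that the software named (SPSS 16.0) can fit the frailty or robust Cox model and the small-sample degrees of freedom; if not, another package should be named.

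### Under the plan's general rule, urine protein-creatinine ratio would get an unadjusted t-test; if the ratio is right-skewed, a log-scale analysis with the month-0 value as covariate is more efficient at patient level

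*Protocol article*

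**What the plan says.** The Outcomes section of the protocol article states: "The secondary outcomes are laboratory parameters (Table 4) and incidence of clinical endpoints". Table 4 (Clinical and laboratory assessments) lists "Urine protein -creatinine ratio" at month 0 and every three months from month 3 to month 24, nine measurements in all. It lists 24-hour urine protein at months 0, 6, 12, 18 and 24.

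The Statistical analysis section has one rule for continuous variables. They are summarised so: "Descriptive statistics will be expressed as the mean and standard deviation". They are compared so: "An independent t-test will be applied to compare mean values and mean differences between intervention and control groups". Only the rate of eGFR decline is given a model. For laboratory values the section names no transformation, rank test or baseline covariate. It adds: "All statistical tests will be two-tailed tests" and "A P-value of less than 0.05 will be considered statistically significant".

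Two figures bear on the range of the ratio. The exclusion in Enrollment is "urine protein-creatinine ratio more than 3.5 g/g creatinine", and the treatment target in Table 2 is "Less than 500 mg/g".

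**The concern.** A protein-creatinine ratio cannot fall below zero, and entry is allowed up to seven times the treatment target (3.5 / 0.5 = 7). In a mixed population with diabetes and/or hypertension, a few heavily proteinuric patients could dominate raw means and standard deviations. If they do, an unadjusted t-test on raw values or raw changes is inefficient against a proportional reduction, and mean with SD describes the data poorly. The month-0 value, which could absorb much of the variation between patients, would not be used as a covariate. At stake is the chance of detecting a real effect on one secondary outcome. The primary eGFR analysis is not affected.

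**Working it through.** **The plan's own figure.** The only sample size calculation is for the eGFR slope: 2 × (1.960 + 0.842)² × 3.8² / 1² = 226.7, so 227 per group by the normal approximation and 228 with the t distribution. The stated 228 reproduces. It says nothing about the protein-creatinine ratio, for which the article gives no mean, SD or power.

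**Inputs from the article.** 433 enrolled; 15% loss; entry cap 3.5 g/g; two-sided 5% level.

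**Assumed inputs.** Equal split, giving 433 × 0.85 / 2 = 184 per arm; log-normal ratio with median 0.3 g/g, cut at 3.5 g/g at baseline only; correlation 0.7 between baseline and follow-up on the log scale; proportional reduction of 30%; log-SD varied; one follow-up value; no clustering.

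**Power by simulation, 30% reduction:**

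| Log-SD | Raw values, t-test | Raw change, t-test | Log values, t-test | Log value with baseline covariate |
|---|---|---|---|---|
| 0.5 | about 100% | about 100% | about 100% | about 100% |
| 0.8 | 96% | 97% | 99% | over 99% |
| 1.0 | 81% | 87% | 93% | over 99% |
| 1.3 | 55% | 62% | 78% | 96% |

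For a 20% reduction at log-SD 1.0 the same four columns read 43%, 50%, 57% and 85%.

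**Closed-form check of the last column.** SE = log-SD × √(1 − 0.7²) × √(2/184), and the effect is |ln 0.7| = 0.357.
- Log-SD 1.0: SE = 1.0 × 0.714 × 0.1043 = 0.0745; 0.357 / 0.0745 = 4.79; power = Φ(4.79 − 1.96) = 99.8%.
- Log-SD 1.3: SE = 0.0968; 0.357 / 0.0968 = 3.69; power = Φ(1.73) = 96%.

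**Type I error without clustering.** With no treatment effect, all four methods reject in about 5% of runs.

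**Effect of one district per arm.** Assume an ICC of 0.01 on the log scale, as a district shift in the follow-up value.
- Log values, unadjusted: design effect 1 + 183 × 0.01 = 2.83; true error of a nominal 5% test = 2 × [1 − Φ(1.96 / √2.83)] = 24%.
- Log value with baseline covariate: patient-level variance falls to 0.51 of its size but the district shift does not, so the factor is about 1 + 184 × 0.01 / 0.51 = 4.6 and the error is 2 × [1 − Φ(1.96 / √4.6)] = 36%.
- Raw values: a little under 20% by simulation.

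**24-hour urine protein.** The Laboratory analysis section has two of twelve subgroups per group collect it. At 25 to 30 patients per subgroup (Sample size section) that is nominally 50 to 60 per arm, so the table does not apply. With 50 per arm, log-SD 1.0 and a 30% reduction, power is about 31% for raw values, 36% for raw change and 68% for the log value with baseline covariate.

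**The case against.** The strongest objection is that the article never names the test or the scale for this ratio. The rule is general, a t-test on log values would comply with it, and transforming one laboratory variable could be left to a fuller document. It stands this far: a reader might infer that the plan expressly commits the ratio to a raw-scale t-test, and the text does not say so. But the ratio has no other rule to fall under, mean with SD points to the raw scale, and an unadjusted t-test on either scale leaves out the baseline covariate. The point proposes a better method in place of a stated one. It does not complain of missing detail.

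Second, a reader might take strong skew as established. It is not. The documents give no distribution, the entry cap trims the upper tail at baseline, and at log-SD 0.5 the methods hardly differ.

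Third, mean differences may be read as changes from baseline. That reading already uses the month-0 value by subtraction and has 97% or 87% power at log-SD 0.8 or 1.0. The shortfall is then serious only with wide spread or a smaller effect.

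Fourth, two changes are combined. Baseline adjustment on the raw scale alone gives about 99.7%, 93% and 67% at log-SD 0.8, 1.0 and 1.3. Both steps contribute, and the log scale matters most where the spread is wide.

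Fifth, with one district per arm, district and treatment effects cannot be separated, and cutting patient-level noise raises the false-positive rate of a patient-level test. This stands in full. It limits what any such p-value can mean, but it is a separate defect of the design and no reason to prefer the less efficient summary.

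**Conclusion.** The point holds as a recommendation on efficiency for a secondary outcome. By the general rule the ratio gets an unadjusted t-test, with no log scale and no month-0 covariate. If log-SD is 0.8 to 1.3, a log-scale analysis adjusted for baseline recovers, for a 30% reduction, roughly 4 to 41 percentage points of patient-level power over raw values (from 96% to over 99%; from 55% to 96%) and roughly 3 to 34 points over raw change (from 97% to over 99%; from 62% to 96%). These figures rest on the assumed median, spread, correlation and effect, on an equal split of 433 patients, and on ignoring clustering.

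Three stronger conclusions are not supported. Skew does not make the planned t-test invalid at this size, since its error rate is about 5% without clustering. The change is not free, because it replaces a difference in arithmetic means by a ratio of geometric means. And the gain does not make the comparison more trustworthy: with one district per arm, patient-level p-values remain anticonservative on either scale, more so after baseline adjustment.

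**What to change.** In the Statistical analysis section, state that the natural log of urine protein-creatinine ratio is analysed with the month-0 log value as covariate, that the result is reported as a ratio of geometric means with its confidence interval, and that the ratio is described by median and interquartile range. Do the same for 24-hour urine protein, noting that only two of twelve subgroups per group collect it. Add that, with one district per arm, patient-level intervals and p-values do not account for variation between districts.

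The cost is a few sentences, with no extra patients, visits or samples. The downsides are a changed estimand, the need to state a floor for values below the assay limit, and the clustering caveat, which this change cannot remove.
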